### Participants

Participants for stages 1 and 3 will be recruited from a population of patients under physicians specialising in the care of patients with difficult-to-treat asthma at Glenfield hospital, Leicester, UK, and will have had a thorough diagnostic assessment and appropriate treatment strategy instituted prior to recruitment. They will be identified as eligible if they have:
Symptomatic asthma despite being on step 4–5 treatment according to SIGN/BTS guidelines^31^ (high-dose inhaled corticosteroids (>1000 µg beclomethasone equivalent) plus a second controller and/or systemic corticosteroids);Been treated under the care of a difficult-to-treat asthma specialist for at least 6 months.

Participants will be excluded if they:
Have a diagnosis of smoking-related COPD;Have both fixed airflow obstruction (FEV_1_/FVC <70%) and a smoking history of ≥10 pack years;Are unable to exercise—for example, due to significant musculoskeletal or neurological abnormality;Have a history of significant cardiac disease—for example, myocardial infarction (MI) within the last 3 months, unstable angina or heart failure, and/or significant valvular disease;Had a severe exacerbation of asthma in the preceding month prior to entry to the programme;Had a hospital admission due to an exacerbation of asthma within the last 3 months;Had an ITU admission involving intubation within the last year.

Informed written consent from potential participants will be obtained by the research team.

### Stage 1

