#### A small-scale version of an RCT trial of asthma-tailored PR versus UC in individuals with severe asthma

##### Study design

A small-scale RCT will be conducted to assess feasibility of a large multicentre trial. A maximum of 60 patients will be recruited. Participants will be randomised to either the asthma-tailored PR group or UC group using internet-based ‘sealed envelope’ randomisation codes as advised by our local clinical trials unit. Randomisation to treatment group allocation will be a 2:1 ratio (asthma-tailored PR:UC) as retention rate is the primary outcome rather than effectiveness. Randomisation allocation is sent by automated email to unblinded research team members (data will be collected and analysed prior and immediately post intervention and at 6-month follow-up (figure 1)).

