##### Safety

Any adverse events directly or indirectly related to the exercise measurements and training sessions will be recorded. Any severe adverse event will be reported to our research and development office immediately. An external respiratory physician has agreed to independently assess any adverse events and stop the trial, if necessaryA full cardiopulmonary exercise test with expiratory gas analysis will be performed on a treadmill.^43^ Exercise-induced bronchoconstriction will be assessed by a flow-volume loop, before and after the treadmill test. This data will be used as an outcome measure not just for safetyAsthma control and disease activity will be assessed by the ACQ, measuring airway inflammation by induced sputum count before and after the intervention and by comparing the preceding 9 months unscheduled healthcare visits for asthma with 9 months after and including the intervention including GP, accident and emergency attendance and hospital admissions

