##### Exacerbation of asthma

Patients will be asked to keep a diary of their exacerbations, treatment and unscheduled healthcare visits. The patients will be asked to stop coming to the asthma-tailored PR sessions for any exacerbation requiring steroid treatment. If they are not recovered enough to start participation within 2 weeks, they will be classified as dropout. Similarly, they will be excluded from the UC limb if they are not back to normal within 2 weeks to avoid bias.

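### The 9-month before-after comparison of unscheduled asthma visits uses a 'before' window that eligibility partly empties of admissions, and the Safety section states no correction and no usual-care contrast

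*Protocol article*

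**What the plan says.** The Safety section of Stage 3 lists how asthma control and disease activity will be assessed. For healthcare use it does so "by comparing the preceding 9 months unscheduled healthcare visits for asthma with 9 months after and including the intervention". GP visits, A&E attendances and hospital admissions all count. The section does not name the usual-care arm for this measure and mentions no adjustment.

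The Participants section excludes a patient who meets any of these criteria:
- "Had a hospital admission due to an exacerbation of asthma within the last 3 months"
- "Had a severe exacerbation of asthma in the preceding month prior to entry to the programme"
- "Had an ITU admission involving intubation within the last year"

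It also requires the patient to have "Been treated under the care of a difficult-to-treat asthma specialist for at least 6 months".

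Under Exacerbation of asthma, the protocol says: "Patients will be asked to keep a diary of their exacerbations, treatment and unscheduled healthcare visits". The same section removes patients who have not recovered from an exacerbation within 2 weeks: they count as dropouts in the PR arm and are excluded from the usual-care arm. Statistical analysis is descriptive.

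**The concern.** A before-after comparison is fair only if an event could be counted equally well in both windows. Here the entry criteria clear the most recent part of the 'before' window of the events being counted, while the 'after' window carries no such restriction. Part of any rise in admissions would then come from selection.

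The case for the trial is that evidence on the safety of exercise in severe asthma is sparse, and this measure sits under Safety. A rise that comes from eligibility could be read as harm, and a real reduction could be hidden. Reporting the figures only descriptively does not prevent either misreading.

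**Working it through.** The documents give no figure for healthcare use, so there is none to reproduce.

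**Inputs**
- Window length: 9 months before and 9 months after (Safety).
- Admission-free period: last 3 months. Severe-exacerbation-free period: last 1 month. Free of intubated ITU admission: last 12 months (Participants).
- Planned numbers: 40 PR and 20 usual care. Assumed dropout 25%; local PR dropout about 15% (Sample size calculation).
- Assumptions not in the documents: the 'before' window ends at entry, the event rate is constant over time, follow-up is complete, and the admission rate lies between 0.3 and 2.0 per patient-year.

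**Eligibility effect.** With no true change, the expected ratio is the number of months in which an event can occur after entry divided by the number before.
- Admissions: 9/(9 − 3) = 9/6 = 1.50.
- Visits due to severe exacerbations, apart from admissions: at most 9/(9 − 1) = 9/8 = 1.125.
- Intubated ITU admissions: none is possible in the 'before' window.

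The 1.50 does not depend on the rate or on variation between patients, because the same selected patients supply both windows. Simulation with Poisson and gamma-Poisson counts, conditional on no admission in the last 3 months, gave 1.495 to 1.501 over the assumed rates.

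**In events.** With no variation between patients, the spurious excess in 40 PR patients is 40 × rate × (0.75 − 0.50) = 10 × rate. That is 3 admissions at 0.3 per year and 20 at 2.0 per year. With variation between patients, the lowest simulated value was 2.6.

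**Masking.** A true rate ratio of 0.80 would show as 0.80 × 1.50 = 1.20. A true ratio of 2/3 would show as 2/3 × 1.50 = 1.00.

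**Forces in the other direction** (sizes are assumptions)
- Months 7-9 before entry may precede specialist care. If the rate then was m times the later rate, the ratio is 9/(3m + 3): 1.20 for m = 1.5, 1.00 for m = 2, and 0.75 for m = 3.
- If a fraction d leaves at about 6 weeks (1.4 months) and contributes no later events, the ratio is [9(1 − d) + 1.4d]/6. For d = 0.25 this is (6.75 + 0.35)/6 = 1.18. For d = 0.15 it is (7.65 + 0.21)/6 = 1.31.

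**Between-arm alternative.** Both arms pass the same entry filter, so it cancels: 1.50/1.50 = 1.00 under no effect, and (0.80 × 1.50)/1.50 = 0.80 when the true ratio is 0.80.

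**The case against.** The strongest reply is that the Safety section describes what is measured, not the whole analysis. The trial is randomised 2:1, the diary is not limited to one arm, and a before-after change in each arm, compared between arms, would fit the wording. The article is condensed and the SAP is not shown. A rise in both arms would itself expose the artefact. This stands against one tempting inference, that the randomised control is unused for this measure. The text does not name usual care here, but it does not rule out a between-arm contrast. What the reply does not remove is that the one comparison the article states is before versus after, with no mention of the admission-free months.

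Three other stronger readings also go beyond the documents:
- **A net false rise is certain.** Only the eligibility component is known to be upward. Earlier non-specialist care and the removal of unrecovered patients can offset or reverse it.
- **All unscheduled care is inflated by half.** The 1.50 applies to admissions. GP and A&E visits that do not lead to admission are touched only through the 1-month rule.
- **ACQ and sputum will regress to the mean.** Entry requires symptomatic asthma but sets no ACQ or sputum threshold, and it excludes recent exacerbators, which favours recent stability. Both measures are listed as secondary outcomes of the randomised trial, so the before-and-after wording for sputum reads as a measurement schedule.

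It is also fair to say that the stakes are limited. Unscheduled visits appear in neither the primary nor the secondary outcome list. Safety rests mainly on adverse-event incidence, which an external physician assesses independently.

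**Conclusion.** The point holds for the comparison as stated. Eligibility leaves 6 of 9 'before' months open to an admission, so the expected after/before ratio with no effect is 1.50 for admissions, and at most 1.125 for other visits due to severe exacerbations. These figures assume a constant rate, complete follow-up and a 'before' window that ends at entry. The net bias could be up or down, so the before-after figure cannot be read as evidence of harm or of safety. For a descriptive measure in a feasibility trial, outside the listed outcomes, the severity is moderate to minor.

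**What to change.** - State that unscheduled healthcare use is compared between asthma-tailored PR and usual care over the same 9 months from randomisation, as events per patient-time by arm with a 95% CI.
- Follow removed or withdrawn patients for healthcare use where possible; otherwise count only their observed time. Removal follows an exacerbation, so observed-time rates need that caveat in both arms.
- Keep before-after figures as description only. Express 'before' admissions per month at risk (6 months) and state the eligibility artefact beside them.

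**Cost.** This takes a few sentences of wording. The diary appears to supply the data in both arms, but following removed patients would add some collection, since the protocol now reports only data gathered up to withdrawal.

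The downside is an imprecise comparison. As an illustration, take equal Poisson rates and complete follow-up. Expected events are then 40 × 0.75 × rate = 30 × rate and 20 × 0.75 × rate = 15 × rate, and the standard error of the log rate ratio is √(1/(30 × rate) + 1/(15 × rate)) = √(0.1/rate). At an assumed 1 admission per year this is 0.316, so the 95% limits lie a factor of exp(1.96 × 0.316) ≈ 1.86 either side of the estimate. At 0.3 per year the factor is about 3.1, and at 2.0 per year about 1.55. Variation between patients would widen these limits.

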##### Cost-effectiveness

The EuroQol^54^ questionnaire will be used to assess quality-adjusted life-years (QALYs) at baseline, 12 weeks and 9 months. Costs will be calculated using NHS tariffs. All treatment including medication, adverse events and any over-the-counter medication will be recorded.

##### Exacerbation of asthma

Patients will be asked to keep a diary of their exacerbations, treatment and unscheduled healthcare visits. The patients will be asked to stop coming to the asthma-tailored PR sessions for any exacerbation requiring steroid treatment. If they are not recovered enough to start participation within 2 weeks, they will be classified as dropout. Similarly, they will be excluded from the UC limb if they are not back to normal within 2 weeks to avoid bias.

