##### Intervention (asthma-tailored PR)

Asthma-tailored PR will be based on a traditional PR programme but will be exclusively for severe asthma. It will be undertaken in a hospital setting in case of adverse events. The programme will extend over 12 weeks with two supervised, 2 h sessions per week (1 h of exercise and 1 h of multidisciplinary education) and a well-defined home exercise programme. A rolling programme will be used and the duration of the programme may have to be extended for return after exacerbations.

For the exercise component, combined endurance and strength training will be based on our local successful PR programme and evidence-based international guidelines for PR and health.^38^
^39^ An exercise prescription includes intensity, frequency, mode and duration, but there is little specific guidance for asthma^38^
^40^ other than high-intensity aerobic training^41^ (60–80% of peak oxygen consumption (VO_2_ peak) or peak heart rate). We propose predominantly high-intensity walking-based endurance training, as our local preliminary data were successful.^28^ We will aim for an initial walking duration between 6 and 10 min to be increased to 20–30 min over 1–4 weeks aiming for an end Borg Score for breathlessness of 4–6.^42^ The speed of the walk will be recalibrated at 4 and 8 weeks, where needed. It is anticipated that fast walking will be high-intensity exercise for this population, but cycling or jogging will be prescribed if needed. A home walking diary will be kept and participants advised to walk daily. Strength training will comprise upper and lower limb exercises: two sets of 6–12 repetitions at 80% one repetition maximum for knee extensors and flexors on the gym equipment and elbow flexion and extension using free weights. The programme above is a preliminary design and any part of this will be adapted for the feasibility study according to the results of stages 1 and 2.

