##### Outcome measurements

The primary outcome measures are:
Recruitment rate (incorporating willingness of patients to be randomised and practicality of a hospital-based programme);Retention rate (incorporating acceptability of the therapy);Incidence of adverse events.

We will record the time to recruit and complete the trial.

The secondary outcome measures are:
Exercise capacity assessed by both laboratory treadmill testing (and optional cycle ergometer),^43^ (including exercise-induced bronchoconstriction^44^ and dynamic hyperinflation) and field testing by both ISWT^45^ and the endurance shuttle walk test (ESWT).^46^ The repeatability of the ISWT in this population will also be assessed.Sputum eosinophil count,^47^ exhaled nitric oxide and inflammatory markers in the blood.Asthma control using the Asthma Control Questionnaire (ACQ).^48^HRQoL using the Asthma Quality of Life Questionnaire (AQLQ)^49–51^ and Chronic Respiratory Questionnaire.^52^Psychological morbidity using the Hospital Anxiety and Depression Scale.^48^Quadriceps strength assessed by an adapted chair with a strain gauge^53^ and body composition assessed by dual-energy X-ray absorptiometry (DEXA).^53^Domestic physical activity measured by tri-axial accelerometers (Sensewear pro 3).^52^

The outcome measures to assess the intervention will be collected at baseline, 12 weeks and 9 months by a blinded investigator (see figure 1 for study schedule). Baseline demographics will be recorded including body mass index (BMI) and spirometry. To promote participant retention and follow-up, all the study visit dates and times will be arranged at the participant's convenience during the first visit. They will receive a reminder telephone call the day before their visit. In the event of participant's withdrawal, any data collected prior to that point will be reported.

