##### Sample size calculation

The primary outcomes for the feasibility study are recruitment, retention and incidence of adverse events, to establish the practicality of a definitive multicentre RCT. We plan to recruit 40 patients to the intervention arm and 20 patients to UC. We estimate conservatively that we will recruit 30% of those invited to estimate the recruitment rate with a precision of at least ±7%. We suggest a conservative dropout rate of 25% (our local PR dropout rate is approximately 15%); recruiting 40 patients to the asthma-tailored PR programme, the precision of the estimated retention rate would be at least ±14%.^55^ From experience to date, we are expecting very few serious adverse events relating to the exercise programme. Based on a rate of 2.5%, the rate would be estimated to be less than 13%.^56^ All precisions are based on two-sided 95% CIs.

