##### Statistical analysis

Data collected will be entered to a secured local database by the researchers. A descriptive analysis will be performed using mean (SD) and median (IQR) for normally and not normally distributed variables, respectively. The recruitment and retention rates will be described as percentages.

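### The 2-week exacerbation rule drops PR patients and excludes randomised usual-care patients for slow recovery alone; this does not avoid bias and clouds the retention outcome

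*Protocol article*

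**What the plan says.** The protocol article, under Exacerbation of asthma, asks PR patients to stop attending for any exacerbation that needs steroids. It then states: "If they are not recovered enough to start participation within 2 weeks, they will be classified as dropout". For the control arm it adds: "Similarly, they will be excluded from the UC limb if they are not back to normal within 2 weeks to avoid bias".

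Other sections bear on the rule:

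- Outcome measurements lists as a primary outcome "Retention rate (incorporating acceptability of the therapy", in brackets. It schedules assessments at baseline, 12 weeks and 9 months. For participants who withdraw, it says that "any data collected prior to that point will be reported".
- Sample size calculation plans on 25% dropout among 40 PR patients and goes straight from that to the precision of the retention rate, so dropout is treated there as the complement of retention.
- Statistical analysis says: "The recruitment and retention rates will be described as percentages".
- Safety includes "comparing the preceding 9 months unscheduled healthcare visits for asthma with 9 months after and including the intervention".
- Intervention notes that "the duration of the programme may have to be extended for return after exacerbations".

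**The concern.** The rule acts on randomised patients after randomisation, and its trigger is a disease event that the trial itself records through the diary, the unscheduled visits and the ACQ. Applying it to both arms does not make it neutral. Exercise training may change how often patients exacerbate or how fast they recover, so those left in each arm need not be comparable. The two thresholds also differ: fitness to resume sessions in PR, full return to normal in UC.

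Two results are at stake. The first is retention, which the Dissemination section names among the measures that decide whether the definitive trial can be done. A PR patient who wants to continue but needs three weeks to recover counts the same way as one who rejects the programme. The second is the 9-month comparison of unscheduled visits. If patients removed by the rule are no longer assessed, those with the slowest-recovering exacerbations drop out of a safety measure.

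**Working it through.** **1. The plan's own figure.** Inputs from Sample size calculation: n = 40 PR patients, 25% dropout, two-sided 95% CI, stated precision at least ±14%.

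Wald half-width = 1.96 × √(0.75 × 0.25 / 40) = 0.134, or 13.4 points. The exact interval for 30/40 is 58.8% to 87.3%. The stated precision reproduces; the question is what the percentage counts.

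**2. Effect of the rule on PR retention.** One patient classified as a dropout moves retention by 1/40 = 2.5 points. Suppose the planned 0.25 × 40 = 10 dropouts occur and k of them were willing patients caught by the rule. Retention as the protocol counts it is 30/40 = 75% for every k. Retention counting only the other losses is (30 + k)/40:

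| k (assumed) | As counted | Without rule-based dropouts |
|---|---|---|
| 0 | 75% | 75% |
| 2 | 75% | 80% |
| 4 | 75% | 85% |
| 6 | 75% | 90% |
| 8 | 75% | 95% |

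For scale, k = 4 shifts the figure by 4 × 2.5 = 10 points, the gap between the planned 25% dropout and the roughly 15% quoted for the local PR programme. With k = 6 the shift is 15 points, more than the stated ±14%. The documents give no value for k; the table shows sensitivity and is not a forecast.

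**3. Effect on UC retention.** The planned arm size is 20. PR patients are called dropouts, UC patients are called excluded, and the article does not say how exclusion enters the rate. As an assumed example, let 5 of 20 leave, 2 of them through the rule:

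- Excluded patients counted as lost: 15/20 = 75%.
- Excluded patients taken out of the denominator: 15/18 = 83.3%.
- Rule not applied and those 2 followed up: 17/20 = 85%.

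The same events give three retention figures. Under the second convention the arms would also be counted differently, because PR dropouts stay in their denominator.

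**4. Follow-up.** The sections on exacerbation, withdrawal and safety, set side by side, leave a gap. The rule removes patients by classification or exclusion. The withdrawal sentence covers data already collected. The safety comparison needs nine months of data. None of them says that a patient removed by the rule is still assessed at 12 weeks and 9 months, and none says that assessment ends. Loss from the safety comparison is therefore conditional.

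**The case against.** There is a fair case on the other side, and several stronger readings go too far.

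- **A reader might infer that the trial will report one undivided retention figure with no reasons for loss.** The text does not support that. It says only that rates are given as percentages, and a breakdown by reason is commonly left by a condensed article to the full protocol or SAP. The exacerbation diary and the Stage 3 interviews could also help to identify the cause of a loss. The missing breakdown is not part of this point.
- **A reader might infer that a PR dropout leaves the trial and is no longer assessed.** The article does not say so. The withdrawal sentence concerns participants who withdraw, and it does not say that later data are refused.
- **A reader might put the UC effect at 5 points per patient (1/20).** That holds only if excluded patients count as lost, which is not stated.
- **Retention is said to incorporate acceptability, not to equal it.** Inability to continue because of exacerbations is real feasibility information. That is correct, and it is a reason to record such events in their own right.
- **A limit on pauses is reasonable and compatible with extending the programme.** This also stands. What is hard to defend is turning the limit into dropout or exclusion.
- **The numbers may be small.** Eligibility excludes a severe exacerbation in the preceding month and an asthma admission within 3 months, which may limit early events. No count is available either way.

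What remains is the rule as written: recovery time alone decides, and randomised UC patients are excluded for a reason that does not hold.

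**Conclusion.** The point holds in limited form. The protocol fixes a post-randomisation exclusion in UC and a dropout classification in PR, both on slow recovery and with unequal thresholds, and excluding patients in this way does not avoid bias. Three consequences follow, with different degrees of certainty:

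- Each willing PR patient caught by the rule lowers PR retention by 2.5 points. This follows from the text, on the Sample size section's use of dropout as the complement of retention.
- UC retention is ambiguous, because the status of excluded patients in the denominator is not defined.
- The 9-month unscheduled-visit comparison loses the slowest-recovering patients only if assessments stop.

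The total effect cannot be sized without a slow-recovery rate. The 25% dropout is a planning input for precision and not a pass mark, so no feasibility decision is shown to turn on the rule. In a descriptive feasibility trial this is a change worth making, somewhere between one to consider and one that should be made.

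**What to change.** Replace the 2-week rule in Exacerbation of asthma as follows:

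- **PR:** record failure to resume within 2 weeks as a programme interruption for exacerbation, with dates and whether the patient returned, and not as dropout. Whether and when sessions restart, using the programme extension already foreseen, stays with the investigators.
- **UC:** record slow recovery as an exacerbation event, with no exclusion from the arm.
- **Both arms:** keep every randomised patient in the retention denominator, and assess each at 12 weeks and 9 months unless the patient withdraws.
- **Reporting:** give trial retention by arm, and exacerbation-related programme interruption as a separate figure.

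The cost is revised wording for both arms and one extra case-report category. The main drawback is that some 12-week assessments will fall before an interrupted programme is complete; recording the interruption dates lets readers see which ones.

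### A slow-recovering exacerbation takes randomised participants out of usual care and makes them dropouts in rehabilitation; this does not avoid bias, and it blurs the primary retention rate.

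*Protocol article*

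**What the plan says.** The *Exacerbation of asthma* section of the protocol article (Stage 3) asks PR participants to stay away from sessions during any exacerbation that needs steroids. It then sets a rule for each arm:

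- PR: "If they are not recovered enough to start participation within 2 weeks, they will be classified as dropout".
- UC: "Similarly, they will be excluded from the UC limb if they are not back to normal within 2 weeks to avoid bias".

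Four other places bear on this:

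- *Outcome measurements* lists as primary outcomes "Retention rate (incorporating acceptability of the therapy" and "Incidence of adverse events". The same section states: "In the event of participant's withdrawal, any data collected prior to that point will be reported".
- *Safety* limits event recording: "Any adverse events directly or indirectly related to the exercise measurements and training sessions will be recorded". It also plans to assess asthma control by "comparing the preceding 9 months unscheduled healthcare visits for asthma with 9 months after and including the intervention".
- *Cost-effectiveness* collects EuroQol at baseline, 12 weeks and 9 months.
- *Intervention (asthma-tailored PR)* says that "the duration of the programme may have to be extended for return after exacerbations".

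*Statistical analysis* reports retention as a percentage. It does not say whether an excluded UC participant stays in the denominator.

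**The concern.** The trigger is a slow-recovering exacerbation after randomisation. That is a disease-control outcome, which the trial tracks through the diary, the Asthma Control Questionnaire (ACQ) and unscheduled care. Selecting on it makes the remaining groups differ from those randomised, which is the opposite of the stated purpose.

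Two things are at stake. The first is retention, one of the rates on which, according to *Dissemination*, the decision about a definitive trial will rest. A person willing to continue and to attend visits is recorded as a dropout or excluded because the protocol says so, and the rate then no longer separates acceptability from illness. The second is follow-up. If a removed participant is not seen again, the later ACQ, EuroQol, diary and healthcare-use data are missing for those with the worst course.

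**Working it through.** **1. The two rules side by side.**

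| | PR | UC |
|---|---|---|
| Test at 2 weeks | well enough to take part again | back to normal |
| Consequence | counted as a dropout | excluded from the arm |
| Period in which it applies | not stated; tied to sessions | not stated |

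On its wording the UC test is the stricter one. A dropout can remain in the denominator and count against retention, whereas someone excluded from an arm may leave the denominator.

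**2. The plan's own figures** (*Sample size calculation*: 40 PR, 20 UC, 25% dropout, two-sided 95% intervals).

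- Retention 30/40 = 75%. Wald half-width = 1.96 × √(0.75 × 0.25 / 40) = 0.134, or 13.4 points. This agrees with the stated ±14%.
- Serious adverse events 1/40 = 2.5%. The Wilson upper limit is 12.9%, which agrees with the stated limit of less than 13%.

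These figures are not in dispute. They give the scale for what follows.

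**3. Effect on retention.** The share removed by the rule is not in the document. I assume 0 to 15% of those randomised, and that those removed would otherwise have been retained.

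| Assumed share removed | PR, counted as dropouts | UC, counted as dropouts | UC, taken out of the denominator |
|---|---|---|---|
| 0% | 30/40 = 75.0% | 15/20 = 75.0% | 15/20 = 75.0% |
| 10% (4 PR, 2 UC) | 26/40 = 65.0% | 13/20 = 65.0% | 13/18 = 72.2% |
| 15% (6 PR, 3 UC) | 24/40 = 60.0% | 12/20 = 60.0% | 12/17 = 70.6% |

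At 10%, PR retention falls by 10 points, against a planned precision of about 14. If UC exclusions leave the denominator while PR cases stay in it, a gap of 72.2 − 65.0 = 7.2 points appears between arms that are identical by construction.

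If removal is instead independent of other dropout, the PR fall at 10% is smaller: 0.75 × 0.90 = 67.5%.

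**4. Safety, as a risk only.** If one further serious event in a removed PR participant went unrecorded, an observed 1/40 would truly be 2/40 = 5.0%. The Wilson upper limit would then be 16.5%, not 12.9%. Nothing in the document shows that this would happen.

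**The case against.** The case for the plan has real substance.

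- **PR participants are not removed from the analysis.** They are called dropouts and can stay among the 40. This stands. Only the UC wording speaks of exclusion, so a reader who inferred that the rule decides who is analysed in both arms would go beyond the text.
- **Earlier data are kept.** The triggering exacerbation precedes removal, and the article says that data before a withdrawal are reported. It does not say whether a protocol exclusion counts as a withdrawal, but nothing says that earlier data are discarded. What may be lost is later follow-up.
- **Primary safety is largely untouched.** A reader might infer biased adverse event results in both arms. Recording concerns events linked to exercise tests and training. UC has no training sessions, and a PR participant who has stopped is no longer exposed to them. Events at later exercise tests could be missed, which is a risk and no more.
- **The windows may match.** A reader might infer that the rule runs for 12 weeks in PR and 9 months in UC, and model a large between-arm distortion in exacerbations. The text fixes neither window, and its linking word could mean the same period in both arms. Such a model would also need exacerbation rates that the document does not give, and would need pre-removal data to be thrown away.
- **This is a feasibility study with descriptive analysis.** Its 25% dropout allowance already exceeds the local 15%. With 15% other dropout and 10% of the remainder removed, retention is 0.85 × 0.90 = 76.5%, still above the planned 75%. The allowance may therefore absorb the effect on numbers. It does not restore the meaning of the rate.
- **Inability to resume can fairly count as non-retention in the programme.** This is a defensible definition if it is labelled as such and kept apart from leaving the trial.

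**Conclusion.** The point holds in a limited form and should be fixed. Excluding UC participants after randomisation on a disease outcome is wrong as written, and the stated reason for it is mistaken. Because the arms have different tests and different consequences, the retention rates are not defined alike, and rule-driven stops are mixed with acceptability. Later data on the patients doing worst can be lost.

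The size cannot be determined from the document. Under the assumed 0 to 15% removed, PR retention reads between 75% and 60%. UC retention reads between 75% and 60%, or between 75% and 70.6%, depending on the denominator. These figures assume the planned 25% dropout from other causes and that those removed would otherwise have stayed. Bias in the primary safety result is possible but not established.

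**What to change.** Reword the one paragraph and add a retention definition:

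1. Delete the exclusion from the UC arm.
2. Record non-return to sessions as stopping the programme, separately from leaving the trial.
3. Invite every randomised participant in both arms to the scheduled 12-week and 9-month visits, and continue diary and healthcare-use collection.
4. Analyse everyone as randomised, with one denominator definition for both arms.
5. Report rule-driven stops by arm, apart from voluntary dropout.

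The clinical rule on suspending sessions is not judged here and can stay as it is. The 2-week dropout classification and the statement that the programme may be extended for return after exacerbations must, however, be reconciled.

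The cost is small: a short amendment, and visits that are already scheduled. The downside is that some assessments will be made in less well patients or be deferred.
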